### Data Collection and Data Management

Data are collected through the medical record and patient visits. A study database with all included patients is generated, and the study-specific randomization module and variables from separate case report forms are entered into an electronic data set based on EpiData software, version 3.1 (EpiData Association). Consent and case report forms are locked in a research cabinet accessible to study researchers only and will be retained for 15 years after trial completion at Beijing Chaoyang Hospital. Quality control procedures are applied. All data will be merged at study end and exported to a database for further analysis.

### Outcomes

The primary outcome in this study is the incidence of emergence delirium within 1 hour after tracheal extubation measured using the validated Chinese version of the CAM-ICU.^36^ The CAM-ICU was validated against the *Diagnostic and Statistical Manual of Mental Disorders* (Fifth Edition) criteria for delirium in PACU settings based on the guideline.^38^ With a specificity of 98% and low sensitivity, we may detect the positive delirium cases conservatively in this study.^39^ The positive CAM-ICU test result requires the presence of (1) acute changes in mental status with a fluctuating course and (2) inattention, with either (3) disorganized thinking or (4) altered level of consciousness. Patients with delirium may display hyperactive or hypoactive signs. Hyperactive delirium is defined as RASS scores from 1 to 4, and hypoactive delirium is defined as RASS scores from −3 to 0.^40^ Secondary outcomes include (1) incidence of postoperative delirium within 3 days after surgery (defined as positive CAM-ICU test result); (2) nausea and vomiting within 3 days after surgery; (3) postoperative pain intensity at PACU discharge and 24, 48, and 72 hours after surgery, measured using the visual analog scale (scores range from 0-10, with higher scores indicating greater pain); (4) adverse events (cardiac arrhythmias, cardiogenic shock, and other unexpected adverse events) within 3 days after surgery; (5) length of hospital stay; and (6) all-cause mortality during hospitalization.

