### Intervention and Study Visits

#### Baseline Hospital Ward Visit

Baseline assessments are conducted in the hospital ward. Demographic information, medical history, health history (eg, long-term alcohol use and smoking status), hearing and vision measurement, baseline laboratory tests, and electrocardiography are collected from the electronic medical record. One day before surgery, patients undergo assessments, including pain measured by a visual analog scale,^28,29^ depression by the 9-item Patient Health Questionnaire,^30^ anxiety by the 7-item Generalized Anxiety Disorder Scale,^31^ insomnia by Insomnia Severity Index,^32^ and cognitive function by the Montreal Cognitive Assessment,^33^ with the aim of identifying risk factors of emergence delirium. All planned study visits are presented in the Table.

**Table. zoi200508t1:** The Schedule of Planned Investigation

Study component	Visit 1	Visit 2	Visit 3	Visit 4	Visit 5	Visit 6	Visit 7	Visit 8
Time	1 d before surgery	Before anesthesia	During anesthesia	PACU	POD 1	POD 2	POD 3	Hospital discharge
Eligibility screen	X	−	−	−	−	−	−	−
Informed consent	X	−	−	−	−	−	−	−
Demographic characteristics	X	−	−	−	−	−	−	−
Randomization	X	−	−	−	−	−	−	−
Intervention	−	X	−	−	−	−	−	−
MoCA	X	−	−	−	−	−	−	−
VAS	X	−	−	X	X	X	X	−
PHQ-9	X	−	−	−	−	−	X	−
GAD-7	X	−	−	−	−	−	X	−
ISI	X	−	−	−	−	−	X	−
EEG frequency spectrum	−	X	X	X	−	−	−	−
Blood draw for biomarkers	−	X	−	X	−	−	−	−
CAM-ICU	−	−	−	X	X	X	X	−
Nausea and vomiting	−	−	−	X	X	X	X	−
Adverse events	−	−	−	X	X	X	X	−
Hospital stay	−	−	−	−	−	−	−	X

Abbreviations: CAM-ICU, Confusion Assessment Method for the Intensive Care Unit; EEG, electroencephalography; GAD-7, 7-item Generalized Anxiety Disorder Scale; ISI, Insomnia Severity Index; MoCA, the Montreal Cognitive Assessment; PHQ-9, 9-item Patient Health Questionnaire; POD, postoperative day; VAS, visual analog scale; X, present; minus sign, absent.

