### Intervention and Control

After randomization, patients enrolled in this trial come to the operating room and undergo standard monitoring, including electrocardiography, blood pressure, and oxygen saturation. Intravenous access is then established. The intervention group receives a 5-mg dosage of tropisetron as a bolus intravenously once before induction of anesthesia, whereas the control group receives placebo of 0.9% saline solution. Patients in both groups receive general anesthesia and tracheal intubation. Mean artery blood pressure is maintained above 65 mm Hg during surgery, and the bispectral value is maintained at 40 to 60. Electroencephalographic data are acquired by the bispectral monitoring system for the entire duration of the operation. Information is collected on surgical and anesthesia techniques used (eg, intraoperative medication, anesthesia methods, type of surgery, laparoscopic or open procedure, duration of surgery, estimated blood loss during surgery, intraoperative infusion, blood transfusion during surgery, and patient-controlled analgesia). Patients are transferred to the PACU after surgery. Patients in both groups receive nondrug interventions in the postoperative period. The Enhanced Recovery After Surgery pathway is not applied in our study.

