### Safety and Adverse Event Reporting

The research team is monitoring the study for adverse events. Because the 5-mg dosage of tropisetron is commonly used to prevent nausea and vomiting in the perioperative period, serious adverse events attributable to tropisetron treatment are less likely to occur in the present study. The following adverse events will be reported: those possibly related to the study drug, such as headache, dizziness, diarrhea, and anaphylaxis, and serious events, including death and life-threatening events. Study oversight is performed by an independent data safety monitor board, composed of 2 physicians and a statistician. Interim analyses will be performed for safety concerns after including 500 and 1000 participants.

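### Scheduled adverse-event collection and secondary outcome 4 start after surgery, although the drug is given before induction, so events between injection and the end of surgery fall outside the defined between-arm comparison

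*Protocol article*

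**What the plan says.** Timing of the drug: the Intervention and Control section gives tropisetron "as a bolus intravenously once before induction of anesthesia", with saline as the control. The visit table under Baseline Hospital Ward Visit places the intervention at Visit 2, before anaesthesia.

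Timing of adverse-event collection: the same table marks adverse events at Visits 4 to 7 (PACU and postoperative days 1, 2 and 3). The row begins "Adverse events − − − X X X X", and the table's key defines the minus sign as absent. Visit 2 (before anaesthesia) and Visit 3 (during anaesthesia) both carry it.

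Outcome: in the Outcomes section, secondary outcome 4 is "adverse events (cardiac arrhythmias, cardiogenic shock, and other unexpected adverse events) within 3 days after surgery". Under Secondary Outcome Analysis, adverse events are compared between groups with a chi-square or Fisher exact test.

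Safety reporting: the Safety and Adverse Event Reporting section says that the team monitors for adverse events. It will report "those possibly related to the study drug, such as headache, dizziness, diarrhea, and anaphylaxis", together with serious events, among them death and life-threatening events. No time window is attached. An independent board oversees the trial, with interim safety analyses at 500 and 1000 participants.

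Eligibility: exclusion criterion 7 in Eligibility Criteria is a severe adverse event during the operation, with cardiac arrest as the example.

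**The concern.** The drug is given once, and the whole operation lies between that dose and the first visit at which adverse events are scheduled. The table and the outcome definition agree on this, so it does not look like a slip in a single table cell. For a one-dose intravenous drug, the interval just after the injection belongs in any comparison of tolerability.

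At stake is what the adverse-event result would mean. If outcome 4 is analysed as defined, a finding of no difference between arms would describe the postoperative period only. It would say nothing about arrhythmias or reactions during induction and surgery, although arrhythmia is named in the outcome itself and anaphylaxis is named in the safety section. Readers would probably take the result to cover the whole period since dosing.

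**Working it through.** The article gives no figure to reproduce and no arithmetic bears on the point. The check is to set the statements side by side in time order.

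1. **Visit 1, day before surgery.** The table marks randomization here. Adverse events: absent.
2. **Visit 2, before anaesthesia.** The table marks the intervention here, and Intervention and Control confirms a bolus before induction. EEG and a blood draw are also marked, so this is an active study visit. Adverse events: absent.
3. **Visit 3, during anaesthesia.** EEG is marked, so study data are being taken. Adverse events: absent.
4. **Visits 4 to 7, PACU to postoperative day 3.** Adverse events: present at all four.
5. **Visit 8, discharge.** Adverse events: absent. Hospital stay is recorded.

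Adverse events are thus scheduled at 4 of 8 visits. Of the visits from dosing to day 3 (Visits 2 to 7, six in all), the two without adverse-event collection are the dosing visit and the anaesthesia visit.

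**Outcome definition against the schedule.** Outcome 4 counts from surgery onward. It therefore agrees with the table and leaves out the same interval, from injection to the end of surgery.

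**Intraoperative data.** Intervention and Control says that "Information is collected on surgical and anesthesia techniques used" and gives examples such as medication, type and duration of surgery, blood loss and transfusion. No adverse event is among them. Because these are only examples, their silence supports the reading but does not prove it.

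**Safety section against outcome 4.** The safety section makes anaphylaxis and life-threatening events reportable at any time, whereas outcome 4 counts events only once surgery is over. An anaphylactic reaction at injection is therefore reportable under one section and outside the defined outcome under the other.

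**Exclusion 7 against the sequence.** A severe intraoperative event can occur only at Visit 3, after randomization (Visit 1) and dosing (Visit 2). The criterion cannot work as a screen before entry. The Statistical Analysis section defines nonadherence as failing to receive the intervention or placebo. A dosed patient with such an event is not nonadherent by that definition, and no other rule in the article says how the patient is handled.

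**The case against.** The strongest reply is that the article does provide for these events. The safety section sets no time limit on monitoring or reporting and names anaphylaxis. Data Collection and Data Management lists the medical record as a source, so an entry made in the PACU could include an event that began earlier. Patients have ECG, blood pressure and oxygen saturation monitoring, and unblinding for safety is allowed. The article is also condensed, and onset rules for adverse events may be in the full protocol.

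Much of this stands, and it rules out several stronger readings that a reader might be tempted to draw:

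- **That adverse events are recorded only from PACU to day 3.** The open-ended reporting commitment contradicts this. What is limited is the scheduled collection and the defined outcome.
- **That the board's interim reviews omit the intraoperative period.** The article does not tie those reviews to outcome 4 or to the table. It does not say what data they use.
- **That severe intraoperative events vanish from the trial.** Life-threatening events are reportable, an intraoperative death would count under in-hospital mortality, and the primary analysis follows intention to treat. The article does not say that such patients' safety data are discarded.
- **That the two event lists conflict, that only drug-related events are compared, or that stopping at day 3 is an error.** Outcome 4 includes other unexpected events and has no relatedness filter. The safety section gives examples and also covers serious events without an end date. Deaths are already followed to discharge. Ending routine follow-up at day 3 after one dose is a design choice.

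The reply does not dispose of the core point. Ad hoc reporting does not replace a defined window for comparing arms, and the window that is defined leaves out dosing and anaesthesia. Nor is this a detail left to another document: the article states the window and marks the two visits as absent.

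**Conclusion.** The point holds as an inconsistency in the safety window. The adverse-event schedule and secondary outcome 4 both begin after surgery, while the drug is given before induction. The safety section names an acute drug reaction and life-threatening events as reportable without that limit. Exclusion criterion 7 adds to the gap because it can take effect only after dosing and its consequence for the safety comparison is not stated.

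The interval from injection to the end of surgery is affected in every dosed patient. The article gives no event rates or onset times, so no count of uncounted events can be given, and none is claimed. The point concerns the adverse-event comparison. It does not affect the definition of the primary outcome or the sample size calculation.

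The conclusion assumes that outcome 4 and the table are applied as worded. If the full protocol already starts adverse-event collection at the injection, then the article's outcome definition and table are what need correcting.

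**What to change.** Reconcile Eligibility Criteria, the visit table, Outcomes, and Safety and Adverse Event Reporting, as follows:

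1. Define secondary outcome 4 as adverse events from study-drug administration to postoperative day 3.
2. Mark adverse events at Visits 2 and 3 in the table.
3. State that a randomized and dosed patient who has a severe intraoperative event stays in the between-arm safety comparison, whatever exclusion criterion 7 is meant to do.
4. State that the data given to the board at 500 and 1000 participants cover the period from dosing, and include those patients.

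The cost is wording in the protocol and case report form, plus abstraction of intraoperative events. Trial Status says that recruitment is under way. For patients already enrolled, events can be taken from existing anaesthesia records, in both arms alike and by staff blinded to allocation. This assumes that those records were kept as part of routine care, which the monitoring described in Intervention and Control makes likely. No extra patient contact is needed.

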### Sample Size Calculation

The sample size calculation is based on the primary outcome. According to previous studies, the incidence of delirium diagnosed in the PACU ranged from 3.7% to 22.2%.^7,8,9^ We assumed an emergence delirium incidence of 15% in the control group and a 6% reduction (the clinical limit of superiority) in the intervention group. With a power of 80% and 1-sided α = .05 and using superiority tests for 2 proportions, 640 patients per group are required. With a dropout rate of 15%, the final planned total sample size is 754 randomized patients in each group. The sample size calculation was performed on PASS software, version 14.0 (Number Cruncher Statistical Software).

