### Primary Outcome Analysis

The primary outcome of our analysis is the incidence of emergence delirium. Comparisons in delirium incidence between the 2 groups will be assessed with a χ^2^ test, and 95% CIs will be calculated for the difference in delirium incidence.

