### Secondary Outcome Analysis

For secondary outcome analyses, the Mann-Whitney test will be used for length of hospital stay, whereas the χ^2^ test or the Fisher exact test will be used for categorical variables, including incidence of postoperative delirium within 3 days after surgery, nausea and vomiting, postoperative pain, and adverse events. For analysis of all-cause mortality during hospitalization, we will use Kaplan-Meier curves, with a log-rank test for between-group comparison. The Cox proportional hazards model will be used to estimate the hazard ratio among patients in the tropisetron group compared with the placebo group with adjusting for potential confounding factors.^42,43^

All statistical tests will be 2 sided, and statistical significance will be defined as *P* < .05. Statistical analysis will be performed with SPSS software, version 22.0 (SPSS, Inc).

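### The sample size of 640 per group does not belong to the planned primary test, and the 6-point assumed reduction is mislabelled as a limit of superiority

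*Protocol article*

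**What the plan says.** All references are to the protocol article.

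- **Sample Size Calculation, effect.** "We assumed an emergence delirium incidence of 15% in the control group", together with "a 6% reduction (the clinical limit of superiority) in the intervention group". One figure is thus both the assumed effect (15% to 9%) and a limit.
- **Sample Size Calculation, test and number.** "With a power of 80% and 1-sided α = .05", and "using superiority tests for 2 proportions, 640 patients per group are required". No separate margin is given. After a 15% allowance for dropout, "the final planned total sample size is 754 randomized patients in each group".
- **Primary Outcome Analysis.** "Comparisons in delirium incidence between the 2 groups will be assessed with a χ^2^ test". A 95% CI for the difference is also planned, but it is not compared with 6 points or any other value.
- **Secondary Outcome Analysis, closing paragraph.** "All statistical tests will be 2 sided, and statistical significance will be defined as *P* < .05".

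**The concern.** In ordinary statistical usage, a limit of superiority is a value that the effect must exceed before superiority is claimed. The analysis sections contain no such value: their null is zero difference. The label therefore does not fit the test that will be run. The sidedness also differs between sizing and analysis, and the number of patients does not follow from the inputs printed beside it.

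Two things are at stake. First, the stated justification for 640 per group cannot be reproduced, and the 80% power attached to it is not the power of the planned test. Second, a reader of a positive result could take it to have cleared a stated clinical limit when only zero has been excluded.

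**Working it through.** **Inputs.** From Sample Size Calculation: p₁ = 0.15; p₂ = 0.15 − 0.06 = 0.09, reading 6% as percentage points; power 80%; 1-sided α = .05; dropout 15%. From Randomization and Blinding: 1:1 allocation. From the analysis sections: χ² test, 2-sided .05. The normal approximation is used throughout.

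**Step 1. Try to reproduce 640 with a null of zero.**

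The unpooled formula is n = (z_α + z_β)² × [p₁(1−p₁) + p₂(1−p₂)] / (p₁−p₂)². The variance term is 0.15×0.85 + 0.09×0.91 = 0.1275 + 0.0819 = 0.2094.

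- 1-sided: (1.645 + 0.842)² × 0.2094 / 0.06² = 359.6, so 360 per group.
- 2-sided: the same with 1.960 in place of 1.645 gives 456.5, so 457 per group.

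The pooled-variance formula gives 362 (1-sided) and 460 (2-sided). With continuity correction these become 395 and 493. None is near 640.

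**Step 2. Try other readings of the inputs.**

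| Reading | n per group |
|---|---|
| 6% as a relative reduction (15% vs 14.1%), 1-sided / 2-sided | 18,979 / 24,094 |
| 6% as the treated rate (15% vs 6%), 1-sided / 2-sided | 143 / 181 |
| 15% vs 9%, 1-sided, 95% power | 633 |
| 15% vs 9%, 2-sided, 90% power, continuity correction | 648 |

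The last two come near 640, but only by contradicting the stated 80% power.

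**Step 3. Test whether 6 points can be a margin.** With a margin M, the denominator becomes (p₁ − p₂ − M)². For M = 0.06 it is (0.06 − 0.06)² = 0, so no finite n gives 80% power. Power stays at α, 5% 1-sided, whatever the enrolment. With a 6-point margin, 640 per group would give 80% power only if the true treated rate were about 4.9%, a reduction of about 10.1 points. The document does not assume this.

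**Step 4. Find a margin that fits.** For M = 0.015, n = (1.645 + 0.842)² × 0.2094 / 0.045² = 639.3, so 640. Neighbouring margins give 612 (1.4 points) and 669 (1.6 points). This keeps every stated input and adds one number that the document does not contain.

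**Step 5. Power of 640 per group for the planned test.** The pooled standard deviation term is √(2×0.12×0.88) = 0.4596 and the unpooled term is √0.2094 = 0.4576.

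- 2-sided .05: z = (0.06×√640 − 1.960×0.4596) / 0.4576 = (1.518 − 0.901) / 0.4576 = 1.35, so power is about 91%.
- 1-sided .05: the same with 1.645 gives z = 1.67, so power is about 95%.

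**Step 6. Dropout.** 640 / 0.85 = 752.9, so 753 against the stated 754. That step is sound.

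**Step 7. What P < .05 would show.** At 640 per group with 15% in control, the χ² test is first significant at 96 vs 72 events. That is a reduction of 3.75 points, with a 95% CI of about 0.06 to 7.4 points. Such a result excludes zero and little more.

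**The case against.** The strongest defence is that this is loose wording. The governing verb in Sample Size Calculation is that the reduction was assumed, and the bracket merely glosses it as the smallest worthwhile difference. The success rule appears once and is consistent: a 2-sided χ² test at .05. The Conclusions section frames the hypothesis as a decrease in incidence, with no minimum. Much of this stands.

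A reader might infer that the plan contains two rival null hypotheses. On that reading, observed reductions between about 3.75 points and about 9.4 points (where the 95% CI would first exclude 6) would succeed under one rule and fail under the other, and the sponsor could choose after seeing the data. The documents do not support this. Nowhere do they state a 6-point null, a decision rule at 6 points or a second test. A significant result below a target difference is ordinary in a superiority trial, and a 6-point margin would make the stated power impossible.

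The 1.5-point margin is also open to challenge. If the margin is left free, some value will match any number above about 360, so a round value is suggestive and not proof. The full protocol in the Supplement, which is not at hand, may record what was entered.

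What the defence does not answer is the arithmetic. If 6 points is only the target, the stated inputs give about 360 or 460 per group, and 640 remains unexplained.

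**Conclusion.** The point holds in limited form. The printed sizing does not match the planned primary test in sidedness, power or number, and the limit label on the 6-point figure is wrong for that test. The stated 640 per group exceeds the 2-sided pooled requirement by 640 − 460 = 180 patients per group. It carries about 91% power for 15% vs 9%, where the text states 80%.

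The error does not leave the trial underpowered for its own target. The damage is to reproducibility and to how a positive result will be read. These figures assume 640 evaluable patients per group, a 15% control rate and a 6-point absolute reduction. That a margin of about 1.5 points was used in the sizing software is an inference only, and the verdict does not depend on it.

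**What to change.** In Sample Size Calculation:

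1. Call the 6 points the assumed (target) absolute difference and remove the limit label.
2. State that the primary null is a risk difference of zero, tested 2-sided at .05, in agreement with the two analysis sections.
3. Disclose any superiority margin entered in the sizing software, and say that the primary test does not use it.
4. Restate the power of 640 evaluable patients per group for that test: about 91% for 15% vs 9%.

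In Primary Outcome Analysis, say that P < .05 is reported as a difference from zero alongside the 95% CI already planned, and not as exceeding a clinical limit. A 6-point margin should not be added to the test, since power under the trial's own assumption would then be about alpha.

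The cost is wording in the protocol and analysis plan before unblinding, with no change in enrolment or data collection. The downside is that a significant result can no longer be described as having exceeded a clinical limit of superiority.

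### The 640 per group cannot be reproduced from the printed inputs, which give about 360; for the planned test 640 gives about 91% power, not 80%

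*Protocol article*

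**What the plan says.** The Sample Size Calculation section of the protocol article gives these inputs:

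- Control rate: "We assumed an emergence delirium incidence of 15% in the control group".
- Effect: "a 6% reduction (the clinical limit of superiority) in the intervention group".
- Error rates and method: "With a power of 80% and 1-sided α = .05 and using superiority tests for 2 proportions, 640 patients per group are required".

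A 15% dropout allowance then takes the figure to 754 per group, 1508 in total. No superiority margin separate from the 6% is given, and no treatment-arm rate other than the one implied by the reduction (9%).

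For the analysis, the Primary Outcome Analysis section says: "Comparisons in delirium incidence between the 2 groups will be assessed". The method is a chi-square test, with a 95% confidence interval for the difference in incidence and no margin. The Secondary Outcome Analysis section closes by making every test two-sided at the .05 level.

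**The concern.** A reader should be able to put the printed inputs into a standard two-proportion formula and recover the printed sample size, allowing for rounding and software variants. Here the printed figure is more than three quarters above the result, which is too large a gap for a choice of variance formula or a continuity correction.

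The wording adds doubt. Calling the 6% "the clinical limit of superiority" is the language of a test against a margin, whereas the planned chi-square test is of no difference. The sample size may therefore have been computed for a different hypothesis from the one to be tested. At stake are the stated basis for enrolling 1508 patients and the meaning of the 80% attached to it.

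**Working it through.** **Inputs, all from the article.** p1 = 0.15; p2 = 0.15 − 0.06 = 0.09; d = 0.06; power 80% (z = 0.8416); one-sided alpha .05 (z = 1.6449), or two-sided .05 as in the analysis (z = 1.9600); 1:1 allocation.

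**Step 1: try to reproduce 640.**

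Unpooled variance: n = (z_α + z_β)² [p1(1−p1) + p2(1−p2)] / d².

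- The variance term is 0.1275 + 0.0819 = 0.2094.
- One-sided: 2.4865² × 0.2094 / 0.0036 = 359.6, so 360.
- Two-sided: 2.8016² × 0.2094 / 0.0036 = 456.5, so 457.

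Other standard versions of the same calculation:

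| Version | One-sided .05 | Two-sided .05 |
|---|---|---|
| Arcsine | 358 | 454 |
| Unpooled | 360 | 457 |
| Pooled | 362 | 460 |
| Pooled, continuity-corrected | 395 | 493 |

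None is near 640; 640/362 = 1.77. Reading the 6% as a relative reduction (15% to 14.1%) moves the other way, to about 18,979 per group.

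**Step 2: check the dropout step.** 640/0.85 = 752.9, so 753 against the stated 754. That step is sound, and the discrepancy arises before it. From 362 the same step gives 426 per group, 852 in total.

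**Step 3: power that 640 evaluable per arm provides, with no margin.** Power = Φ{[d − z_α √(2p̄(1−p̄)/n)] / √([p1(1−p1) + p2(1−p2)]/n)}, with p̄ = 0.12. The two standard errors are √(0.2112/640) = 0.01817 and √(0.2094/640) = 0.01809.

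- One-sided .05: (0.06 − 1.6449 × 0.01817)/0.01809 = 1.665, power 95.2%.
- Two-sided .05: (0.06 − 1.9600 × 0.01817)/0.01809 = 1.349, power 91.1%.

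**Step 4: reduction from 15% that 640 per arm detects with 80% power.** Solving the same expression for p2:

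- One-sided .05: 15% to 10.4%, about 4.6 points.
- Two-sided .05: 15% to 9.8%, about 5.2 points.

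**Step 5: unstated inputs that return 640.** With a superiority margin m, the denominator in Step 1 becomes (d − m)². At one-sided .05 and 80% power:

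- m = 1.5 points, true rates 15% vs 9%: 6.1826 × 0.2094 / 0.045² = 639.3, so 640.
- m = 6 points, true treated rate 4.9%: the variance term is 0.1275 + 0.0466 = 0.1741, and 6.1826 × 0.1741 / 0.041² = 640.3, which is about 640.

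Without a margin, one gets only near 640, and only by changing the stated power: 633 at one-sided .05 with 95% power, or 648 at two-sided .05 with 90% power and continuity correction. The article states none of these combinations.

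**The case against.** The strongest defence is that nothing was miscalculated. The section names superiority tests run in PASS and speaks of a limit of superiority, and a 1.5-point margin reproduces 640 at exactly the stated alpha and power. The article condenses a full protocol placed in a supplement that is not at hand, and the margin may be stated there. This stands to the extent that an arithmetic slip is not proven. It does not rescue the text: the article prints its inputs and its result, they disagree, and the only figure it calls a limit is 6%, not 1.5%. A margin calculation would also not give the power of the planned test, which has no margin.

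It is also fair to say that the discrepancy does no harm to power. For 15% vs 9% and the planned two-sided test, 640 per arm exceeds the 80% target. That stands, and it limits the point to a correction of the design statement.

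Three stronger readings are tempting, and the documents do not support them:

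- A reader might infer that power is only 5%, taking the 6 points as both the margin and the true effect. At that boundary power equals alpha, and no finite sample reaches 80%, so such a calculation could not have returned 640.
- A reader might infer about 70% power, by applying a 1.5-point margin at two-sided .05. That is the power of a margin test that the article does not plan.
- A reader might infer that a null result could not be interpreted, or that the success criterion is unknown. The planned 95% interval shows which differences are excluded, and the planned test is of any difference.

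**Conclusion.** The point holds as a failure to reproduce and a wrong pairing of power with effect. The printed inputs require about 360 per group (about 460 at the two-sided level of the analysis), not 640. For the planned test, 640 evaluable per arm gives about 91% power for 6 points, or 80% for about 5.2 points; at one-sided .05 the figures are about 95% and 4.6 points. The error overstates the N needed for the stated effect.

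These figures assume that the 6% is an absolute reduction, that the control rate is 15%, that 640 per arm are evaluable, and that the null is no difference. Whether the cause is a slip or an omitted input cannot be settled from the article. The two margin routes in the working are assumptions that happen to fit. Under either, 80% is still not the power of the planned chi-square test.

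**What to change.** 1. Retrieve the PASS inputs behind 640 and disclose any margin and the assumed treatment-arm rate. Do this first, so that the true design basis is not overwritten by a power figure worked out afterwards.
2. Keep N = 1508.
3. Restate the power for the planned test: about 91% for 15% vs 9% at two-sided .05 with 640 evaluable per arm, equivalently 80% for a reduction of about 5.2 points. Write the effect as 6 percentage points.
4. Remove the phrase "the clinical limit of superiority", or explain it, so that the sample size and the primary test address the same hypothesis. If a margin was used, say so, and say how it relates to a primary test that has none.

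The cost is one re-run of the calculation and a few sentences, best settled before unblinding. No patients are added and the trial's conduct does not change.
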